##### The Couplelinks facilitator

Each couple in the treatment group is linked with a facilitator with whom they regularly interact as they proceed through the modules. Interactions with the facilitator predominantly occur through the Couplelinks website ‘Dialogue Room’ (DR). The DR is an asynchronous (facilitator and couple are not online simultaneously) communication platform that utilizes bulletin board technology to enable each partner to correspond directly with their facilitator, as well as with one another, as they progress through the program. Additionally, the facilitator has two pre-arranged phone ‘check-ins’ after module two and four. Each time a couple completes a module their facilitator is notified by an automatically generated email from the website. After reviewing each partner’s online reflections and feedback about the module, the facilitator provides the couple with feedback via the DR in order to validate their insights and new learning, acknowledge any challenges or difficulties they may have experienced, and explain the objectives of the subsequent module and, where applicable, how it builds on previous themes arising for the couple. At this point the facilitator grants the couple access to the next module. Couples also use the DR, for example, to ask questions about the program, to update the facilitator on their progress, or to inform the facilitator of any events that will conflict with an upcoming due date. The facilitator is also available for additional telephone consultations as necessary; however, the pilot study showed such consultations to be rare and, when undertaken, usually done to resolve minor technical issues.

There will be a total of five mental health professionals with experience in psycho-oncology with a range of disciplinary backgrounds (psychology, nursing, and social work) serving as Couplelinks facilitators. The current facilitators have been instrumental in developing this novel form of support and/or are well versed in the principles and techniques of providing Couplelinks facilitation as detailed in the Couplelinks program facilitation manual [98]. In addition to studying the manual, newer members of the facilitation team receive individualized coaching and instruction on how to offer the intervention through ‘role play’ with a trainer (a clinician member of the research team), who acts as a ‘dummy’ couple, progressing through each DLM and interacting online with the training facilitator as an actual couple would.

The program facilitation manual describes in depth the guiding principles for online facilitation for the program overall, and for each of the seven DLMs. It also provides numerous examples of text-based feedback to each module, including facilitator responses to various challenges that may occur, such as a couple whose participation is interrupted due to investigation of a new, concerning symptom. All facilitators are individually supervised by either the first or second author (KF and SA) which includes an ongoing review of their interactions with active couples as logged and visible in the back-end of the Couplelinks interface (described below). All facilitators also attend regular peer supervision teleconference meetings led by the first and second author. Together, both forms of supervision ensure treatment fidelity; that facilitators adhere closely to the principles of online facilitation as articulated in the Couplelinks manual and maintain consistency in their method of facilitation. Which of the five facilitators a couple is assigned to will depend on whether or not the facilitator has space in his or her caseload, the facilitator’s discipline, and the corresponding regulating body’s stance on inter-jurisdictional practices. For instance, a clinical counsellor licensed in British Columbia may serve couples from other provinces, while a psychologist licensed to practice in Ontario cannot facilitate couples who reside outside of his or her geographic jurisdiction.

### Front-end user interface

Every detail of the website, from its ‘look and feel’ to the content, was conceived with an eye toward being inclusive of both genders, clear and easy to follow, and engaging and enjoyable. The homepage includes an introductory video introducing the facilitator. Additionally, each DLM has its own corresponding home page and a video interview of a couple from the phase I trial of Couplelinks sharing their thoughts and reflections on that specific DLM. Another important consideration in the design of the intervention was that it be convenient and adaptable to the demanding schedules of younger couples. Pilot testing indicated that each module takes, on average, one hour in total to complete. In order to assist with planning and time management, an automated scheduler called the ‘Lesson Tracker’ that lists each module, its constituent steps, and estimated time for completion was introduced in the phase III version of the website and located on the homepage. Each time one step of a module is completed it registers automatically in the Lesson Tracker. Partners’ work is saved and they can log back in at a later time and use the Lesson Tracker to locate where they left off. Several optional readings are available on the Couplelinks website that focus on concerns most relevant to younger couples dealing with BC, and relational coping including fertility after BC, coping with premature menopause, sexuality and intimacy during and after treatment, parenting through breast cancer, and living with uncertainty and fears for the future. As not all topics pertain to each couple, there are no required readings.

### Back-end administrative interface

There is an administrative back-end to Couplelinks with different levels of access for each member of the Couplelinks team. The facilitators have access to the module data for the couples they are directly working with, and a ‘contact notes’ section to communicate with the research team overseeing the project. The facilitator uses the administrative interface to review a given couple’s progress on modules and their feedback, as well as to advance the couple to the next module. Additionally, facilitators can log contact notes to describe all interactions that occur outside the Couplelinks website, such as the phone call check-ins or emails that may have been exchanged due to difficulty with the website. The research coordinator ((RC) co-author, AP) and two clinician scientists (KF and SA) who are in charge of overseeing timely completion of modules and supervising facilitators have access to all outcome measure responses, facilitator contact notes, and all entries logged by all participants as they progress through each DLM.

### Confidentiality and security

The website is password protected; users must be authenticated in order to access the website. Additionally, all transmission of content and online interactions are encrypted. All data from the website are backed up on secure servers.

### Phase III: study design

This is a multicenter, national prospective two-arm RCT of Couplelinks. Approximately 80 eligible couples will be randomized to either the treatment condition or a waitlist control condition, using randomized block design with a block size of 2 (1:1), stratified by province of residence. The randomization list is generated using PROC FACTEX in SAS (Statistical Analysis System) version 9.3, SAS Institute, Cary, USA.

This study was approved by the Research Ethics Boards of all participating hospitals and cancer centers, namely Sunnybrook Health Sciences Centre (reference number: 300–2009), York University (reference number: 2010-119), Cancer Care Manitoba - Research Resource Impact Committee (reference number: 2013–017), University of Manitoba (reference number: H2013:119), University of British Columbia - British Columbia Cancer Agency Research Ethics Boards (reference number: H10-00300), and Queen Elizabeth II Health Sciences Centre - Capital Health Research Ethics Board (reference number: CDHA-RS/2010-357).

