### Inclusion and exclusion criteria

The RC completes an eligibility screen with interested participants. Eligible couples are those in which the woman has received a diagnosis within the last 36 months of invasive breast carcinoma (non-metastatic), or ductal carcinoma *in-situ*, at or before the age of 50 years. While we did not have specific criteria for stage of cancer treatment, we inform potential participants when they contact the RC for information about the project that it is probably best to begin at or nearing the end of active treatment. Feedback from phase I suggested that participants are more inclined to participate at this stage, and this finding is supported by evidence indicating that couples are often more vulnerable to experiencing conflict at this time due to differing expectations around recovery from BC [47]. Couples must be in a committed, heterosexual relationship (for example, married, cohabitating, engaged, or steadily dating for at least six months at the time of participation). Both partners must fluently read and write in English and have access to a computer with a reliable internet connection.

Couples are excluded from the study at the eligibility screening stage if: (1) either partner self-reports current suicidal ideation and/or attempts, or a diagnosis of a serious and currently active mental illness such as psychotic disorders, bipolar disorder, depression, or substance abuse that is not being successfully managed with psychiatric treatment, and therefore may potentially interfere with his or her capacity to benefit from the program; (2) the couple is either currently in couple counselling or expresses the intent to undertake counselling during the five-month study period; (3) one or both partners self-report interpersonal violence. If it becomes evident at any point over the course of the couple’s involvement in the program that their relationship distress is so significant that they would not benefit from the program, or their participation is significantly exacerbating rather than mitigating their distress, they are asked to discontinue the project and are referred to a face-to-face couple’s counsellor.

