### Procedure

Once a potential participant (typically the patient rather than the well partner) connects with the RC, she is informed about the nature of the project. This potential participant is asked to discuss the project with her partner and, if both are interested, the RC proceeds with scheduling a phone interview with each partner separately to confirm whether they both meet eligibility criteria. When screening couples, in addition to the inclusion and exclusion criteria previously described, the RC assesses partners’ access to, and comfort with, the internet and whether they are likely to be able to keep up with the weekly time commitment for the program. Partners who anticipate interruptions (for instance due to travel) for a duration longer than two weeks are asked to delay enrolment until after they return. To avoid the confounding effects of other interventions, couples are informed of the expectation that they refrain from participating in couple-related psychosocial interventions until they have completed the five-month study term.

If both participants meet the eligibility criteria, the RC proceeds with the informed consent process over the phone, which includes reviewing the objectives of the study, requirements of the participants, how their information will remain confidential, and participants’ right to withdraw at any time. Any concerns or questions are addressed and if the couple is satisfied, they are told they will be mailed a hard copy of the consent form that we request they review, sign, and return and that they may contact the RC again if they have any further questions. Once the signed informed consent form is received, the couples are randomized to the waitlist or intervention condition.

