Next, each partner is separately emailed a unique personal login ID and password which they use to complete all questionnaires, starting with the baseline questionnaires. The couples in the treatment group complete additional questionnaires as described in the measurement section below. Participants are informed that their responses to the surveys will not be shared with their partner, and they are instructed to complete the surveys without consulting one another. Once the time one (T1) measures are completed, the RC informs participants of their group assignment. Participants assigned to the treatment group are informed of the name of their Couplelinks facilitator. The facilitator schedules a phone meeting with the couple to introduce her or himself, clarify expectations of participants, answer questions, and review important information about the website and the intervention. The facilitator then sends the couple their login instructions via email.

Both groups of participants complete standardized questionnaires online at T1, time two ((T2) at post-treatment for treatment and for waitlist groups, taking place eight weeks after T1), and time three ((T3) three months after completion of T2 measures). Participants in the treatment group are also asked to complete a post-treatment interview at T2. Couples in the waitlist group are given the option of receiving the intervention once they have completed the T3 questionnaires; if they choose to participate in the intervention, their completed T3 questionnaires will be used as their pre-treatment (baseline) measurement, and they will be asked to complete surveys at post-treatment and one last time 3 months after posttreatment.

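### Fixed blocks of 2 within province let anyone who knows the block size and the previous couple's arm deduce up to half of the allocations

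*Protocol article*

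**What the plan says.** The protocol article (Phase III: study design) plans to allocate about 80 couples to the programme or to a waitlist control. It gives the method as "using randomized block design with a block size of 2 (1:1), stratified by province of residence". On the mechanism it says that "The randomization list is generated using PROC FACTEX in SAS". It does not say who holds the list or who releases each assignment.

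One role, the research coordinator, appears at almost every step of entry:

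- Inclusion and exclusion criteria: "The RC completes an eligibility screen with interested participants".
- Procedure: the coordinator assesses "whether they are likely to be able to keep up with the weekly time commitment for the program". Partners who foresee a gap of more than two weeks "are asked to delay enrolment until after they return".
- Procedure: if both partners qualify, "the RC proceeds with the informed consent process over the phone". A paper form is then mailed, and randomization follows its signed return.
- Procedure: the baseline (T1) questionnaires come after randomization. Once they are complete, "the RC informs participants of their group assignment".

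Waitlist couples may take the programme only after T3, so arms cannot stay hidden once announced.

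**The concern.** A block of 2 is the most predictable permuted block there is. Once the first couple of a pair in a province has a known arm, the next couple's arm is fixed before that couple has been screened. Stratifying by province does not help, because the recruiter knows each couple's province.

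This matters when the person who can foresee the slot also has discretion over who enters. The judgement on keeping up with the weekly commitment is open-ended discretion. There are also ordinary pressures that need no bad faith: waitlist couples wait until after T3, and treatment couples need a facilitator with caseload space and a suitable licence (The Couplelinks facilitator). If couples expected to do better tended to enter known treatment slots, the difference in T1 to T2 change would carry that selection. It would be hard to see afterwards. The only expectancy measure, the CEQ, goes to the treatment group alone (Measurement), so the arms cannot be compared on it.

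**Working it through.** **Inputs from the article.** Block size 2, 1:1, within province; about 80 couples (Phase III: study design). Target difference in mean RDAS change 1.8, SD of change 3.4, intracluster correlation 0.3, 36 couples per group (Sample size estimation and data analyses plan). Four named recruiting provinces (Recruitment). Recruitment since April 2011, completion estimated June 2015 (Trial status). The article gives no predictability figure to reproduce; 1.8 serves only as a yardstick.

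**1. Share of allocations determined.** For a 1:1 block of size 2b the share is 1/(b+1).
- Block 2: 1/2 = 50%, or 40 of 80 couples.
- Block 4: 1/3 = 33%. Block 6: 1/4 = 25%.
- Provincial totals are not given. With an assumed split of 39/21/13/7, the second-in-block couples number 19 + 10 + 6 + 3 = 38 of 80, so odd totals change little.

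**2. Best-guess accuracy** (always guess the arm that is behind in the block): [b + (4^b/C(2b,b) − 1)/2]/(2b).
- Block 2: [1 + (4/2 − 1)/2]/2 = 75%, or 60 of 80.
- Block 4: [2 + (16/6 − 1)/2]/4 = 70.8%.
- Block 6: [3 + (64/20 − 1)/2]/6 = 68.3%.
- Unpredictable allocation: 50%.

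Full enumeration of the blocks gives the same figures. They assume that the block size is known and that the previous arm is known in time, so they are upper bounds.

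**3. How often couples overlap.** April 2011 to June 2015 is about 50 months. With 80 couples spread evenly over four provinces (an assumption), each province randomizes 20, one about every 50/20 = 2.5 months. If one province supplied half the couples, the gap there would be 50/40 = 1.25 months. The time from signed consent to completed T1 is not given, so the overlap cannot be quantified. At this pace it need not be large.

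**4. Possible bias.** Let g be the shift in expected RDAS change among couples in a known slot. In expectation half of each arm sits in second-in-block slots.
- Only one arm's slots steered: bias = 0.5 × g.
- Treatment slots shifted by +g and waitlist slots by −g: bias = 0.5g − (−0.5g) = g.

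The value of g is assumed. The range is:
- g = 0.25: 0.125 to 0.25 points, 7% to 14% of 1.8.
- g = 0.5: 0.25 to 0.5 points, 14% to 28% of 1.8.
- g = 1.0: 0.5 to 1.0 points, 28% to 56% of 1.8.

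**5. What a retrospective check can see.** Pooling the arms and comparing second with first slots averages +g and −g to zero, so the check must keep the arms apart. Even then it is imprecise. With 36 couples per arm analysed, there are 18 per arm in each slot type. The SE of the treatment effect in one slot type is √(2 × 3.4² × 1.3/36) = 0.91, and the SE of the difference between slot types is √2 × 0.91 = 1.29. That difference would be g to 2g, or 0.5 to 1.0 points at g = 0.5.

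**The case against.** The strongest reply is that the article nowhere says the coordinator holds the list, performs the randomization or used the block size while recruiting. An article commonly leaves concealment to the full protocol. Steering is also harder than the list of roles suggests. Randomization waits for a signed form returned by post, so the couple largely sets the order after the coordinator's call. Delay is asked only of partners who themselves foresee more than two weeks away. Arms are announced after T1, so a second couple already in process may not yet be predictable. The primary comparison is on change, so selection on baseline level alone does not pass straight into bias. Waitlisted couples have no programme to adhere to, which makes the one-arm case (0.5g) at least as plausible as the two-arm case.

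All of this stands as limits on size and certainty. It does not remove the point. Concealing the list is no cure, because the second allocation follows from the block size and the previous couple's arm, and the coordinator learns that arm in order to announce it. The coordinator is described as a co-author (Back-end administrative interface) of the article that prints the block size, so knowledge of it is plausible, though still an inference. The weakness is therefore a rule that the article fixes, not a detail it leaves out.

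**Conclusion.** The fixed block of 2 within province is a poor choice for a waitlist trial in which one role screens, judges likely adherence, consents and announces the arm. Up to 50% of allocations are determined and up to 75% can be guessed. Both are upper bounds that require knowledge of the block size and timely knowledge of the previous arm. The possible bias is about 0.5g to g; at an assumed g of 0.5 points that is 14% to 28% of the target difference.

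A reader might infer more: that allocation was in fact unconcealed for half the sample, that the coordinator knew every second assignment, or that the result is biased by a stated amount. The documents support none of these. They do not show what the coordinator knew at screening, they describe steps that reduce foreknowledge, and they contain no figure for g. That outcomes are self-reported by couples who know their arm is a separate feature of a waitlist design; block size neither causes nor cures it.

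**What to change.** - **Couples still to be randomized.** Replace the list with randomly varying block sizes (for example 4 and 6) within province, and do not disclose the sizes to anyone who recruits. Have an existing team member outside screening and consent release each assignment, after signed consent and completed T1. A larger fixed block is not enough: block 4 lowers best-guess accuracy only from 75% to 71%. Record the changeover date and do not complete open pairs from the old list.
- **Couples already randomized.** Within second-in-block slots, compare T1 scores and baseline characteristics between arms. Compare the treatment effect in second-in-block with that in first-in-block slots. Keep the arms separate throughout. Report the check as weak: T1 scores do not measure g, and the slot comparison has an SE of about 1.3 points, so a null result does not rule out bias.

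**Cost.** A regenerated list and a small change of duties. Arm imbalance within a province could reach 2 to 3 couples instead of 1, which adjustment for province handles. Because the CEQ now goes only to the treatment group at T1, release after T1 means giving it to both groups at T1 or to treatment couples on release. Recruitment began in April 2011, so the new list may reach few couples; the check on existing data needs no new collection.

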### Inclusion and exclusion criteria

The RC completes an eligibility screen with interested participants. Eligible couples are those in which the woman has received a diagnosis within the last 36 months of invasive breast carcinoma (non-metastatic), or ductal carcinoma *in-situ*, at or before the age of 50 years. While we did not have specific criteria for stage of cancer treatment, we inform potential participants when they contact the RC for information about the project that it is probably best to begin at or nearing the end of active treatment. Feedback from phase I suggested that participants are more inclined to participate at this stage, and this finding is supported by evidence indicating that couples are often more vulnerable to experiencing conflict at this time due to differing expectations around recovery from BC [47]. Couples must be in a committed, heterosexual relationship (for example, married, cohabitating, engaged, or steadily dating for at least six months at the time of participation). Both partners must fluently read and write in English and have access to a computer with a reliable internet connection.

Couples are excluded from the study at the eligibility screening stage if: (1) either partner self-reports current suicidal ideation and/or attempts, or a diagnosis of a serious and currently active mental illness such as psychotic disorders, bipolar disorder, depression, or substance abuse that is not being successfully managed with psychiatric treatment, and therefore may potentially interfere with his or her capacity to benefit from the program; (2) the couple is either currently in couple counselling or expresses the intent to undertake counselling during the five-month study period; (3) one or both partners self-report interpersonal violence. If it becomes evident at any point over the course of the couple’s involvement in the program that their relationship distress is so significant that they would not benefit from the program, or their participation is significantly exacerbating rather than mitigating their distress, they are asked to discontinue the project and are referred to a face-to-face couple’s counsellor.

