### Sample size estimation and data analyses plan

All scale and subscale means and standard deviations will be computed and summarized. The primary hypotheses to be tested are that the degree of change or improvement between T1 and T2 on the RDAS, KMSS, MMQ, and DCI summary scales will be greater for the treatment group relative to the waitlist group. Given that data are non-independent (measurements are of individuals that belong to the same dyad and multiple measures are taken per individual across time) the hypotheses will be evaluated using multilevel models (MLM) [109]. MLM will allow for testing correlations between partners’ outcomes and whether there are differences in treatment effect for the patient versus her partner. The models will also be used to evaluate the degree of sustained change from T2 to T3, and whether treatment effects vary by severity of disease, age, and/or length of relationship, as well as aspects of the intervention such as level of engagement. MLM will also allow us to test whether there are any significant variations in treatment effect between facilitators. The impact of missing data will also be evaluated.

The sample size needed was based upon psychometrics of our primary outcome measure, the RDAS. Assuming a two-sided test, a standard deviation for mean change in RDAS from T1 to T2 equal to 3.4 (standard deviation of RDAS = 7.0, with a correlation of 0.9 between T1 and T2), an intracluster correlation of 0.3, an effect size of 0.5 for mean change of RDAS (difference in group means = 1.8), 80% power, and an alpha of 0.05, 36 couples will be required for each group (PASS, NCSS, Kaysville, USA, cluster-randomization power analysis) [110]. The total sample size was calculated as 36 × 2 × 2 = 144. The sample size will be increased to 160 (40 couples per group) due to an expected attrition of 10% of the participants across time, based on previous research in couples and BC [111]. In addition to the questionnaires, qualitative data will be collected from the open-ended evaluation of each DLM following its completion.

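### Couples whom the programme is making worse are asked to leave the project, not just the modules; this can happen only in the treatment arm and biases the T1 to T2 comparison toward benefit

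*Protocol article*

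**What the plan says.** The rule stands in the protocol article under Inclusion and exclusion criteria. It opens "If it becomes evident at any point over the course of the couple" and goes on to speak of the couple's involvement in the program. It has two triggers:

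- the couple's distress is too great for them to benefit;
- "their participation is significantly exacerbating rather than mitigating their distress".

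In either case "they are asked to discontinue the project and are referred to a face-to-face" counsellor for couples.

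Four other places determine what the rule does to the data:

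- **Waitlist access (Procedure).** "Couples in the waitlist group are given the option of receiving the intervention once they have completed the T3 questionnaires".
- **Monitoring (The Couplelinks facilitator).** "Each couple in the treatment group is linked with a facilitator with whom they regularly interact as they proceed through the modules". No comparable contact is described for waitlist couples.
- **Primary comparison (Sample size estimation and data analyses plan).** The arms are compared on the "degree of change or improvement between T1 and T2 on the RDAS, KMSS, MMQ, and DCI summary scales".
- **Missing data.** Measurement says that attrition and non-compliance are taken into account in the analyses. The analysis section says that the impact of missing data will be evaluated. Neither says whether discontinued couples are still assessed.

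**The concern.** Stopping an intervention and leaving a trial are separate events, and the rule joins them. A couple that deteriorates in the modules is asked to leave, while a waitlist couple that deteriorates equally has no programme to be withdrawn from and goes on to give T2 and T3 scores. The second trigger is worsening of distress during the programme, which is closely tied to the change scores on which the arms are compared.

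Two things are at stake. The treatment effect would be estimated after some of the poorest treatment-arm results had been taken out. And deterioration, an important possible harm of a couple intervention, would be under-recorded in the arm where it needs to be seen.

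**Working it through.** **Step 1: what *project* means.** The rule uses *program* for what the couple is taking part in and *project* for what it is asked to leave. Elsewhere *project* means the study: in Inclusion and exclusion criteria (what callers are told about), in Procedure (whose nature is explained to them) and in Trial status (what recruitment is for). Procedure also expects couples to avoid other couple interventions until the five-month term is over, so referral to a couple counsellor fits exit from the study. Exit is the plain reading, but it is an inference.

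**Step 2: which arm.** The rule operates during the programme. Treatment couples are in it between T1 and T2; waitlist couples have no access before completing T3. Within the randomised comparison the rule can therefore act in one arm only.

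**Step 3: whether the model can repair it.** No outcome assessment is scheduled between T1 and T2. A couple that leaves in between contributes T1 alone. A likelihood-based multilevel model is valid if missingness depends only on observed data. Worsening after T1 is not observed, so the second trigger breaks that condition.

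**Step 4: the plan's own figure.** Inputs from the sample size section: difference 1.8, SD of change 3.4, intracluster correlation 0.3, two-sided alpha 0.05, power 80%, attrition 10%.

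- Individuals per arm before clustering: 2 × (3.4 × (1.960 + 0.842) / 1.8)² = 56.0
- Design effect for two partners: 1 + (2 − 1) × 0.3 = 1.3
- Couples per arm: 56.0 × 1.3 / 2 = 36.4, against 36 stated
- After attrition: 36 / 0.90 = 40, as stated

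The planned size reproduces closely and is not in question here.

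**Step 5: size of the bias.** The SD of a couple's mean change is 3.4 × √(1.3 / 2) = 2.74. Suppose there is no true effect, changes are normal, and k of 40 treatment couples are lost, with no other losses. If the k worst are lost, the treatment mean rises by about 2.74 × φ(c) / (1 − p), where p = k/40 and c is the p-quantile of the standard normal. This gives 0.16, 0.30 and 0.53 points for k = 1, 2 and 4. The formula treats the arm as a large population. Simulating arms of exactly 40 couples (40,000 trials, t-test on couple means) gives slightly less:

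| Couples lost | Selection | Bias (RDAS points) | Share of 1.8 | Chance of false benefit |
|---|---|---|---|---|
| 0 | – | 0 | 0% | 2.5% |
| 1 | worst couple | 0.15 | 8% | 4.5% |
| 2 | worst couples | 0.28 | 15% | 7.3% |
| 4 | worst couples | 0.51 | 28% | 14.7% |
| 1 | correlation 0.5 with change | 0.07 | 4% | 3.3% |
| 2 | correlation 0.5 with change | 0.14 | 8% | 4.1% |
| 4 | correlation 0.5 with change | 0.25 | 14% | 6.0% |

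Four couples is 10% of the arm, which would assign the whole planned attrition to this rule. The correlation of 0.5 and every count of lost couples are assumptions.

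**The case against.** The strongest reply is that loss of data is inferred. No sentence says that questionnaires stop or that these couples leave the analysis, and a condensed article may leave such detail to a fuller document. The first half stands, and the point is worded accordingly. The second half does not dispose of it: the article states a rule whose plain effect is exit from the study, and no analysis plan can recover questionnaires that were never sent.

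The general statements on attrition and missing data are relevant, but they name no method and cannot supply the missing T2 and T3 scores.

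The two triggers also differ. The first concerns how distressed a couple is, and T1 captures that at least in part, so its effect on change scores is less certain. The bias argument rests on the second. Screening at entry, which excludes unmanaged serious mental illness and interpersonal violence, should also keep the number of removals down.

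Three stronger readings are tempting and are not supported:

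- **Removal driven by the outcome scores.** Under Back-end administrative interface, the coordinator and supervisors "have access to all outcome measure responses, facilitator contact notes, and all entries logged by all participants". A reader might infer that removal follows T2 or T3 results. T2 is collected after treatment, so while a couple is in the modules only T1 scores exist. There is accordingly no case for hiding scores from these staff.
- **A larger bias.** A reader might use the RDAS SD of 7.0 as the gap between removed and remaining couples, giving 0.05 × 7.0 = 0.35 points for two couples and 0.10 × 7.0 = 0.70 for four. But 7.0 is the SD of the level, not of change. Even removing exactly the worst couples gives only about 0.28 and 0.51.
- **Deterioration not measured at all.** Couples who remain still complete the relationship measures, and facilitator notes record events. Deterioration is under-recorded, not unrecorded.

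**Conclusion.** The point holds in limited form. As written, the rule asks couples who worsen in the programme to leave the study, and it can do so only in the treatment arm before T3. If T2 and T3 are then not collected, the comparison is biased toward benefit and the planned multilevel model cannot undo it.

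The direction is clear for the worsening trigger and less certain for the trigger based on level of distress. The size is unknown because the expected number of removals is not given. For 1 to 4 of 40 couples it is about 0.07 to 0.5 RDAS points, or 4 to 28% of the 1.8-point target, and the chance of a false finding of benefit rises from 2.5% to between 3.3% and 14.7%. The upper figures need four removals of exactly the worst couples and are a ceiling for that count. The range assumes normal changes, no true effect, and no T2 data from removed couples.

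**What to change.** Leave the clinical rule on stopping and referral as it is, and amend only its consequence for the data:

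- state that these couples stop the modules and not the study;
- send them T2 and T3 on the scheduled dates unless they decline;
- analyse them in their randomised arm, and say that this is a treatment-policy comparison, so that their later scores include the effect of any counselling after referral;
- report their number by arm.

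If collected in full, these data remove the selection described above: in the simulation the bias returns to 0 and the chance of false benefit to 2.5%.

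The cost is a wording amendment and online questionnaires for a few couples. The effect estimate may come out smaller, and it will answer the treatment-policy question rather than describe the programme with no later counselling.
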